### 2.8.2 Diet and Exercise Intervention

In addition, we will investigate the effect of structured diet therapy and exercise counselling for diabetic patients by registered dietitian, on anthropometry measurements including weight, body mass index (BMI), and waist and hip circumference. The intervention group will also receive educational adherence session at each follow-up visit by the same dietician to reinforce optimal diet and exercise for each participant to ensure balanced caloric and mineral intakes and effective lifestyle modification.

Intervention procedure:

A) Dietary and Exercise Assessment

All participants of the control and intervention groups will undergo individual pre-assessment of diet and physical activity using the revised version of the summary of diabetes self-care activities (r-SDSCA) measure questionnaire which consists of two core subscale questionnaires (i.e. dietary and physical activity subscale questionnaires (Appendices 7 and 8) to assess self-care management in patients with diabetes [51]), with adequate internal test-retest reliability and evidence of validity and sensitivity to change [52].

The questionnaire will be completed by a specialised dietitian at the initial visit and at each follow-up visit in the intervention group (or at study exit in the control group) to measure participants’ adherence to diet goals and exercise recommendations in an education session for 30 to 45 minutes.

The scale, utilise the metric “days per week” instead of using percentages to cover diabetes self-care activities and adherence, and the questions should cover the past 7 days. If the patient was sick during the past 7 days, the dietitian will ask them to recollect the last 7 days when they were not sick. Each question uses the number of days per week on a scale of 0–7.

B) Usual Care Diet and Exercise Counselling

After recruitment, study participants in both groups will receive basic diet and exercise counselling, in addition to advice on healthy eating for diabetic patients with printed materials (Appendix 9) as part of usual care in the clinic.

Moreover, both groups will complete a pre-assessment nutrition knowledge questionnaire with eight questions evaluating knowledge of the importance of frequent laboratory blood tests; regularly monitoring of kidney function; recommended dietary allowances of Na, K, and Mg; food sources of these elements; and symptoms of deficiency. Moreover, they will receive educational information based on dietician evaluation as part of routine care in the clinic (Appendices 10 and 11).

Participants in the control group will not receive any advice on carbohydrate calculation, healthy plate model, or specific exercise instructions during the study period. Participants in all groups will be asked to report any modifications in their usual diet or activities throughout the study period.

C) Structured Diet and Dietary Carbohydrate Count Education

The intervention group will receive an educational reinforcement session for a structured diet at each follow-up visit by the same specialised dietitian. Dietitian appointments will be performed concurrently after each follow-up visit to the treating physician appointment to build on physician advice; and included nutrition counselling to reinforce balanced caloric and mineral intake, as well as measuring adherence to structured diet plans.

In the structured diet therapy, the dietitian will set individualised carbohydrate (carb) targets for each participant for eating meals or snacks during the day to cover daily macronutrients, considering the participants’ current eating patterns, food preferences, motivation, and ability to follow the recommended diet.

The total daily calories required by each participant will be calculated according to the United Arab Emirates (UAE) ministry of health and prevention recommendations [53], and based on the basal metabolic rate (BMR) calculations [54] considering the appropriate activity factor based on the participants’ lifestyle and work (Table 2).

Table 2: Calorie-calculation based on BMR and activity factors.

| Lifestyle and exercise frequency | Activity factor |
| --- | --- |
| Sedentary (little or no exercise) | BMR x 1.2 |
| Lightly active (light exercise/sports 1-3 days/week) | BMR x 1.375 |
| Moderately active (moderate exercise/sports 3-5 days/week) | BMR x 1.55 |
| Very active (hard exercise/sports 6-7 days a week) | BMR x 1.725 |
| Extra active (very hard exercise/sports & physical job or 2x training) | BMR x 1.9 |

Basal metabolic rate (BMR) calculations for men and women:

BMR for men= [weight (kg) x 10] + [height(cm) x 6.25] – [age(y) x 5] + 5

BMR for women = [weight (kg) x 10] + [height(cm) x 6.25] – [age(y) x 5] – 161

The calculated amount of carbohydrates will be approximately 4–5 carb exchange for males in their main meals (approximately 60–75 g of carb), and for females 3-4 carb exchange in their main meal (approximately 45–60 g of carb), with one to two carb exchanges in their snacks. As part of the structured diet intervention, participants in the study will be instructed to maintain a daily intake of 75–105 g of carbohydrates for males and 60–90 g of carbohydrates for females, divided between the main meals and snacks based on their basal metabolic rate calculations.

Moreover, participants in the intervention group will receive educational materials on the amount of carbs and calories in food and the different methods of measuring food portions by hand, cups, or spoons and to calculate a portion size of 15 grams of carbohydrate to an equal one serving “exchange” (Appendix 12). In addition, participants will be educated on the use of a healthy plate model to prepare their meals [55]. They will also receive educational materials with photos showing the amount of carbs in bread, cereals, rice, and pasta (Appendix 13).

At each scheduled follow-up visits occurring every 3 months (≥3 scheduled visits during the follow-up period), the dietitian will support the intervention group patients in modifying their structured meal plans and achieving their goals throughout the study period. Moreover, a 15-minute phone coach session once per month will be used to motivate the patients to adhere to their structured meal plans, provide guidance on carbohydrate calculation for any additional food preferences, implement a new structured meal plan, and answer any queries concerning diet or exercise interventions.

Dietary carbohydrate value and daily energy intake will be calculated from the patient’s food log for 3 days including a weekend before the first baseline visit and at study exit for all participants, and before each follow-up visit every 3 months for the intervention group. Participants will be asked to fill the food log with all consumed food and beverages measured by hand, cups, or spoons and by portion, weight, or volume for other individual-serving snacks, foods, or beverages outside the home.

In each food log section, the participants can describe the consumed food or beverage, and any other oil, fats, sauces, or condiments used in preparation or added during food serving, in addition to the time and occasion of each meal or snack. During the session, the research dietitian will review the food logs, clarify any unclear entries or descriptions, and estimates the average daily energy intake and dietary carbohydrate value for each participant.

D) Exercise and Physical Activity Reinforcement Counseling

For each participant in the intervention group, the dietitian will develop individual exercise targets based on their clinical condition and motivation level while taking into consideration each participant’s current eating patterns and willingness to adhere to exercise and lifestyle modifications.

Any identified challenges that limit the patient from being physically active will be discussed with the patient, and an action plan will be discussed with the treating physician and documented in the patient’s file.

Anthropometric measurements will be obtained by registered nurses in the clinic at the time of enrolment, before exiting the study for all participants, and at each follow-up visit for the intervention group. Body weight and height will be measured without shoes using a standard monthly calibrated scale at the Dietitian Office (Tanita Corporation, Japan). The same nurse will measure the patients’ waist circumference just marginally above the hipbone and their hip circumference at the largest part of their buttocks.

In addition, to explore the type of most recurring physical activity in our intervention population, we added additional table to the questionnaire to describe the type of physical activity, intensity of the purposive activity, average number of days per week for each activity, and duration of each activity (Appendix 14).

Furthermore, in the absence of a gold standard to classify physical activity intensities, we will calculate the absolute intensities of the exercise sessions based on the recommendations from the American college of sports medicine and the American heart association [56], and the British Association for cardiovascular prevention and rehabilitation (BACPR) [57]. Each activity will be expressed in metabolic equivalent of task (METs) values and classified as light, moderate or vigorous intensity with Borg’s CR10 scale [58] to provide subjective rating of perceived exertion. Guidelines showed that combining both tools augment the relation between fitness levels and exercise intensity [59]. Moreover, to allow homogeneous and adequate analysis of METs values, the mean duration of the training session from patients’ interview will be considered within three categories: 30 minutes or less = 30 minutes, 31 to 60 = 60 minutes, and > 60 min = 90 minutes.

Besides, we will calculate the average metabolic equivalent of task per week based on the corresponding METs of each activity that match with CR10 intensity score (Table 3) multiply the average duration of activity performed in the number of days of activity performed during the week (For example, walking 3.0 mph with CR10 =4 (moderate), equals to 3.3 MET (code:17190) [60], for 30 min on 3 days per weeks [3.3 MET x 90 min] = 2970 MET-minutes per week).

Table 3: Exercise intensity based on CR10 modified scale.

| CR10 exercise intensity scores | MET equivalents |
| --- | --- |
| Low exercise intensity = 0, 1, or 2 | Light < 3.0 METs |
| Moderate exercise intensity = 3 or 4 | Moderate 3.0 – 6.0 METs |
| High exercise intensity = From 5 to 10 | Vigorous > 6.0 METs |

### 2.8.3 Electrolyte Optimization Including Serum Sodium, Potassium as well as Magnesium Levels

During the follow-up, the intervention group will be evaluated for electrolyte imbalance, particularly Na, K, and Mg levels. The metabolic panel (including serum Na, K, and Mg levels) and eGFR will be measured at baseline and at 3, 6, 9 and 12 months after recruitment. Moreover, participants will be evaluated for symptoms of electrolyte imbalance. In patients with no or minimal symptoms of mild to moderate hyper-, hypo-, or hypernatremia [61, 62] hypomagnesaemia [63] and/or hyper- or hypokalaemia [64, 65], treatment is initiated based on the recommended clinical pathway with the primary goal of preventing or treating life-threatening complications while diagnosing and treating the underlying disease [66-68].

At the end of the trial, we will assess the effect of serum electrolyte level optimization during medical investigation on diabetes management, clinical outcomes, as well as kidney function measured by estimated glomerular filtration rate (eGFR) levels.

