## 1.3 Research Aim, Objectives, and Outcomes

The study explores the possible interventions to improve patients’ therapeutic outcomes by medication adherence, structured diet, and exercise education. The research will investigate the impact of multifactorial interventions by pharmacists and clinical dietitian and electrolyte levels optimisation by physicians on the clinical outcomes in Emirati patients with type 2 diabetes.

The primary outcomes are as follows: (1) to evaluate the impact of pharmacist-led MTM on medications adherence, using a new pharmacist intervention protocol (MPIP), (2) to assess the effect of structure diet and exercise counseling with a specialized dietitian on anthropometry readings and carbohydrate as well as daily energy intake levels compared to control group, and (3) to assess the effect of the multi-factorial interventions on diabetic outcomes, including glycated haemoglobin A1c (HbA1c) level, blood pressure, and lipid profile.

The secondary outcomes are: (1) compare the effect of MPIP on regimen-specific medication possession ratio (MPR), and clinical interventions between both groups, (2) evaluate type, duration, and mean metabolic equivalent of task (METs) of physical activity per week during the follow up period between both groups, and (3) analyse serum electrolyte levels, cardiovascular risk factors, and eGFR levels in both group at study exit.

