## 2.8 Study Procedures

Eligible participants will sign the consent form at the physician’s office, and laboratory results will be recorded as baseline data. If the patient’s medical record does not contain recently updated laboratory tests from the previous three months, laboratory tests will be scheduled for blood sample collection in the clinic and tested in Abu Dhabi Health Services Company (SEHA) central laboratory, and the same process will be performed at the conclusion of the follow-up period after 12 months. Laboratory tests in the study protocol included gylcated hemoglobin A1c (HbA1c), estimated Glomerular Filtration Rate (eGFR), complete blood count, electrolyte panel including potassium and magnesium levels, serum creatinine levels, and albumin/creatinine ratio.

Laboratory and clinical assessments in the study protocol included BP measurement and laboratory tests HbA1c level, low-density lipoprotein cholesterol (LDL-C) level, complete blood count, electrolyte panel including K and Mg levels, eGFR, serum creatinine level, and albumin/creatinine ratio. BP measurements and laboratory tests will be performed according to the standard procedures for BP measurement and blood sample withdrawal at the clinic.

In addition, each participant in both groups will undergo individual assessments at initial visit and study exit including medication adherence by clinical pharmacist and diet and exercise assessment by specialized dietician.

During the study period, the control group will receive the usual care provided in the clinic including the routine follow-up and clinical assessments (as needed). The routine usual care will include follow-up schedule every 3 months with the treating physician, vital signs monitoring in the visited clinic, physician consultation, any additional investigational services or laboratory tests requested by the treating physician depending on each patient’s condition, patient counselling at the pharmacy counter, dietitian counselling service if requested by the patient or referred by the treating physician, and a call reminder from the clinic call centre 3 days before the appointment.

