Moreover, the control group will have their HbA1c levels recorded at least twice yearly (at initial and exit visits) in patients with stable glycaemic control meeting the treatment goals and quarterly in patients not meeting the treatment goals, which will be at the discretion of the attending physician [40]. Other laboratory tests will be performed twice yearly (or more frequently as per the physician’s request), and any major adverse cardiac events, emergency room visits or hospitalisations will be recorded and compared with baseline data.

The intervention group will receive multi-factorial interventions and assessments at initial visit and at each follow-up visit every 3 months after enrolment in the study. The multi-factorial interventions composed of the three below approaches: medication adherence counselling with medication therapy management program, diet and exercise counseling, and serum sodium, potassium and magnesium optimization (Figure 1).

- Adherence and MTM assessment.
- Diet and exercise assessment.
- Clinical outcomes and electrolyte level assessment.

Close-out

12-month visit

12-month visit

- Adherence counselling and MTM.
- Diet and exercise intervention.
- Multifactorial interventions with electrolytes level optimization.

Interventions

6-month visit

3-month visit

1-month visit

9-month visit

- Baseline laboratory tests, Na/K/Mg levels .
- Medication adherence questionnaire.
- Diet and exercise assessment.

Pre-assessment

Initial visit

Initial visit

Eligibility – Inclusion - Randomisation (1:1)

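### Primary outcomes 1 and 2 and the closing sentence of Protocol 2.8.3 credit single components, but the only randomised contrast is the whole programme versus usual care

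*Protocol*

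**What the plan says.** **What is randomised.** Figure 1 in Protocol 2.8 shows two arms allocated 1:1. The intervention is "composed of the three below approaches: medication adherence counselling with medication therapy management program, diet and exercise counseling, and serum sodium, potassium and magnesium optimization", and it goes to the whole arm: "The intervention group will receive multi-factorial interventions and assessments at initial visit and at each follow-up visit every 3 months". Controls receive usual care (2.8). For them this includes baseline counselling by a clinical pharmacist (2.8.1), basic diet and exercise advice with printed material (2.8.2), and a dietitian visit on request or referral (2.8).

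**What is claimed.**
- Primary outcome 1 (1.3): "to evaluate the impact of pharmacist-led MTM on medications adherence". The sentence goes on to cite MPIP.
- Primary outcome 2 (1.3): "to assess the effect of structure diet and exercise counseling with a specialized dietitian on anthropometry readings", and on carbohydrate and energy intake, compared with control.
- Closing sentence of 2.8.3: "we will assess the effect of serum electrolyte level optimization during medical investigation on diabetes management, clinical outcomes, as well as kidney function", with kidney function measured by eGFR.
- Primary outcome 3 (1.3) is worded as the effect of the combined interventions on HbA1c, blood pressure and lipids.

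**What MPIP means.** Section 1.1 uses the label for the combined approach as a whole. Section 2.8.1 uses it for a pharmacy-led programme with two parts, adherence counselling and MTM.

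**What is analysed.** Section 2.10 plans two-group tests (chi-square, t-test, Mann–Whitney) and sizes the trial for differences between the two groups.

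**The concern.** Three statements name one component each as the cause of an effect, and two of them are primary outcomes. The trial never varies one component while holding the others fixed. A difference in adherence could come from MTM, from the added dietitian contact, or from both. A difference in BMI could come from the diet plan or from drug changes made under MTM.

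The electrolyte sentence is the most exposed. Its outcomes (diabetes management, clinical outcomes, eGFR) are ones that the other two components can also plausibly influence.

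At stake is what the trial may conclude. Read literally, the objectives invite conclusions about MTM alone, diet counselling alone or electrolyte correction alone. A clinic could then adopt one component without evidence that it works by itself.

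**Working it through.** The point has no figure of its own in the plan, so the check is one of identifiability.

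**1. Inputs.** Two arms and three components (Protocol 2.8). No single-component, package-minus-one or staggered arm is described. Two-group tests and 90 patients per group (2.10).

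**2. Model.** Let M, D and E indicate assignment to MTM with adherence counselling, to the structured diet and exercise programme, and to electrolyte optimisation, each on top of usual care. The counselling that both arms receive sits in the intercept.

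- Control row (1, M, D, E) = (1, 0, 0, 0), with mean = μ
- Intervention row = (1, 1, 1, 1), with mean = μ + βM + βD + βE, plus any interactions

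With 90 rows of each kind, the matrix has four columns and rank 2. The estimable quantities are μ and the sum βM + βD + βE (with interactions). The separate terms are not estimable at any sample size.

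**3. Illustration on a challenged outcome.** The planned BMI difference is 2.5 (2.10). The splits (βM, βD, βE) = (0, 2.5, 0), (2.5, 0, 0) and (1.25, 1.25, 0) each sum to 2.5 and give the same two arm means. The data cannot favour one over another. The same holds for the MPR difference of 0.035.

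**4. Do the components touch the same endpoints?** The protocol's content makes this plausible, though it gives no size.
- MTM includes changing drug therapy and reviewing for deprescribing (2.8.1).
- Diet is itself a route of electrolyte correction, alongside medication changes (1.1).
- Monthly dietitian calls (2.8.2) come on top of the pharmacist call after each visit (2.8.1).

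**5. Can variation inside the arm help?** All intervention patients have electrolytes monitored, but treatment begins only when an imbalance is found (2.8.3). Treated and untreated patients therefore differ at the outset by the imbalance itself, and that comparison is not randomised.

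**6. What the sample size was built for.** Using n per group = 2(zα + zβ)²(SD/δ)² with 80% power and one-sided 5% alpha, (1.645 + 0.842)² = 6.18:
- MPR: 2 × 6.18 × (0.09/0.035)² gives 82 (stated: 82)
- BMI: 2 × 6.18 × (6.4/2.5)² gives 82 (stated: total 180 after dropout)
- HbA1c: 2 × 6.18 × (1.3/0.5)² gives 84 (stated: 84)

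The figures fit one two-group contrast per outcome. Sidedness is not stated, and two-sided alpha gives 104, 103 and 107. That is a separate matter. Nothing in the sizing provides for component contrasts.

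For scale only, suppose each component alone carried the full stated difference, with 10% dropout and no multiplicity adjustment. Control plus three single-component arms would need 4 × 92 = 368 to 4 × 94 = 376 patients one-sided, or 460 to 476 two-sided. Under the same assumption and with no interaction, a 2×2×2 factorial would need 184 to 188 one-sided, or 230 to 238 two-sided. If a component carried half the difference, 325 to 335 per compared group would be needed one-sided.

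**The case against.** The strongest reply is that the protocol's question is already the package. The aim at the end of 1.1 says so, as does the opening of 1.3. The expected outcomes in 1.4 are stated as intervention against control, and 2.10 sizes the trial for the multi-intervention approach. Outcome 1 cites MPIP, which 1.1 defines as the combined approach, and outcome 2 ends by naming the control group as comparator. On this view, only loose wording in three sentences remains.

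Much of that stands, and it is why the remedy is rewording and not redesign. It does not remove the point. Section 2.8.1 gives MPIP a pharmacy-only meaning, so outcome 1 cannot be relied on to mean the package. Naming the control group as comparator does not change which cause outcome 2 names. Outcome 3 shows that the protocol uses package wording when it means the package.

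It can also be said that refill adherence and carbohydrate intake are direct targets of their own components, so spill-over may be smaller there than for HbA1c. That is plausible, but it is an assumption the design cannot test.

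Some stronger readings are tempting and are not supported:
- A reader might infer that controls receive none of the components. They receive baseline pharmacist counselling and basic diet and exercise advice, so the contrast is an intensified programme against usual care.
- A reader might infer that every intervention patient is treated for electrolytes. Treatment depends on finding an imbalance.
- A reader might infer that the listed electrolyte and eGFR outcome is also at fault. Secondary outcome 3 is worded neutrally as a between-group comparison. The attribution lies only in the 2.8.3 sentence.

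**Conclusion.** The point holds, limited to attribution. Three statements (primary outcomes 1 and 2, and the last sentence of 2.8.3) promise component effects that the single randomised contrast cannot identify. Two quantities are estimable against four parameters, and neither more patients nor a different analysis, including one in an unseen statistical analysis plan, would change this. The inconsistent use of MPIP adds to the ambiguity.

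The conclusion rests on the two-arm structure in 2.8 being complete, with no undescribed arm. It does not depend on how large the cross-effects between components are.

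A reader might go further and infer that the between-arm comparisons of adherence, BMI or eGFR are invalid for this reason. They are not: each can be read as an effect of the whole programme. Nor do the documents show that component conclusions will be published. The objectives permit them, and that is the part to correct.

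**What to change.** Amend Protocol 1.3 and 2.8.3, in line with the aim in 1.1 and with primary outcome 3:

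1. Primary outcome 1: the effect of the whole multifactorial programme versus usual care on medication adherence.
2. Primary outcome 2: the effect of the whole programme versus usual care on anthropometry and on carbohydrate and energy intake.
3. Closing sentence of 2.8.3: the effect of the whole programme versus usual care on electrolytes, clinical outcomes and eGFR.
4. Give MPIP one definition and use it throughout 1.1, 1.3 and 2.8.1.
5. State that no effect of MTM, diet and exercise counselling, or electrolyte correction alone will be claimed, and that any analysis by component received is descriptive.

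The cost is a wording amendment. Arms, procedures, sample size and tests are untouched by this point, and the only downside is narrower claims. A component question would need a different design.
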